# 1. TRIAL SUMMARY

World Health Organization Registration Data Set

| Title | Index microvascular resistance (IMR)-guided management of heart transplantation |
| --- | --- |
| Primary registry and trial identifying number | ClinicalTrials.gov  NCT 06656065 |
| Secondary identifying numbers |  |
| Sources of monetary or material support | No funding. |
| Primary sponsor | Interventional Cardiology Department Miguel Servet University Hospital. Zaragoza, Spain |
| Secondary sponsors (if any) |  |
| Central contact | [name]  Interventional Cardiology Department Miguel Servet University Hospital. Zaragoza, Spain  [name]  [contact] |
| Study officials/Investigators |  |
| Brief title | IMR-HT study |
| Acronym | IMR-HT study |
| Countries of recruitment | Spain |
| Condition(s) or focus of study |  |
| Interventions |  |
| Key eligibility criteria | Age eligibility: 18 years or older  Sex eligibility: Both  Accepts healthy volunteers: No |
| Study design | Study type: Interventional trial  Allocation: Non-randomized  Intervention model: Single group  Primary purpose: Diagnostic  Phase: N/A |
| Masking | None |
| Date of enrollment | March 25, 2024 |
| Target sample size | 100 |
| Recruitment status | Recruiting |
| Primary outcomes |  |
| Secondary outcomes |  |

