## 3.4. Outcomes

- The **primary outcome** of the study is to evaluate IMR values and number of EMB performed in the first year after HT: Depending on IMR values obtained in the first three months, clinical status and the other complementary tests the physician will be able to modify the number of biopsies established in each center protocol.If the IMR is less than 15, the number of biopsies could be reduced or kept the same. If the IMR is 15 or greater,number of biopsies would be performed as usual per protocol.

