## 3.12. Statistical methods

### 3.12.1. Outcomes

The characteristics of the study population will be summarized through standard descriptive statistics. Continuous variables will be expressed as mean (± standard deviation) or median [interquartile range (IQR)], as appropriate. Discrete variables will be presented as absolute numbers and percentages. For the comparison of means, the Student's t test for independent measures or the non-parametric Mann-Whitney U test (in the case of dichotomous qualitative variables) and the ANOVA or non-parametric Kruskal test will be used as a hypothesis test. Wallis (in the case of non-dichotomous qualitative variables). For the bivariate analysis of the qualitative variables, the Chi-square test or Fisher's exact test will be used. Events will be compared between groups by using Kaplan-Meier curves. Cox regression analysis will be performed to adjust for confounding factors and to evaluate independent predictors of clinical events. A two-tailed p-value of 0.05 will be considered statistically significant. All statistical analyses will be performed by SPSS software version 20.

In 2023, around 325 heart transplants were performed in Spain (3). Given a median of 10-15 HT per center and considering that eight centers that routinely perform invasive coronary physiology are participating, data will be analyzed when 100 patients have completed first year follow-up.

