## 4.4. Confidentiality

Sociodemographic, clinical, laboratory and follow-up data of each patient will be included in a database specifically designed for the study. All variables will be included in the online data collection platform Redcap (Research Electronic Data Capture).  Each patient will be assigned a number; their identity will not be revealed in any case. All shared information will be anonymized.

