## 5.3. Roles and responsibilities

### 5.3.1. Protocol contributors

**Index of microvascular resistance (IMR)-guided management of heart transplantation**

**IMR-Heart Transplant Study**

**PROTOCOL**

**SUMMARY**

| **Study title** | INDEX OF MICROVASCULAR RESISTANCE-GUIDED MANAGEMENT OF HEART TRANSPLANTATION |
| --- | --- |
| **Short Running Title** | IMR-HEART TRANSPLANT STUDY |
| **Investigators** | [name]  [name]  [name]  [name] |
| **Study aim** | Follow-up assessment of heart transplant patients based on IMR |
| **Hypothesis** | The index of microvascular resistance will serve to reduce the number of endomyocardial biopsies in transplant patients. |
| **Study design** | Multi-center, prospective, observational |
| **Inclusion criteria** | Heart transplant patients >18 years. |
| **Exclusion criteria** | Patients presenting with hemodynamic instability after HT, including cardiogenic shock or severe coagulopathy. Patients with acute cellular rejection before intracoronary physiological assessment. Patients with bronchial asthma or bronchopathy with a positive bronchodilation test, which contraindicates the use of adenosine. Patients with epicardial coronary lesions with a resting physiological index ≤0.89 or ≤0.80 at hyperemia. Patients unlikely to cooperate in the study or with inability or unwillingness to give informed consent. |
| **Primary endpoint** | Number of biopsies performed in the first year.  IMR in transplant patients, in the first three months and one year. |
| **Secondary endpoints** | Cardiovascular mortality and IMR.  Cardiac allograft vasculopathy and IMR.  Acute cellular rejection and IMR.  IMR variation, in the first two months and at one year.  Combined endpoint of ACR, heart failure, re-transplantation, cardiovascular mortality and IMR.  Immunosuppressive therapy and IMR. |
| **Data analysis** | Observational, analytical |
| **Follow-up** | 1 year and annually for five years |

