**HYPOTHESIS**

Number of EMB performed in the first year post-HT could vary depending on IMR values. Low IMR values in the first three months could reduce the number of protocol EMB. Meanwhile, high IMR values would not modify the number of EMB performed, and could even contribute to intensify immunosuppressive therapy.

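### The only adjusted analysis the protocol names is Cox regression for clinical events; the listed tests that fit the first-year biopsy count by IMR group are unadjusted, although the groups are not randomised.

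*Protocol*

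**What the plan says.** The embedded protocol's SUMMARY table states the hypothesis: "The index of microvascular resistance will serve to reduce the number of endomyocardial biopsies in transplant patients". Its HYPOTHESIS section gives the direction: "Low IMR values in the first three months could reduce the number of protocol EMB", while high values leave the number unchanged. The SUMMARY table lists as a primary endpoint "Number of biopsies performed in the first year", alongside the IMR values. Section 1 records the design as a single group with "Allocation: Non-randomized". IMR of 15 or more counts as high.

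For comparing means between two groups, section 3.12.1 offers the Student "t test for independent measures or the non-parametric Mann-Whitney U test". It then lists ANOVA or Kruskal-Wallis, chi-square or Fisher, Kaplan-Meier curves and, as the one adjusted method, "Cox regression analysis will be performed to adjust for confounding factors and to evaluate independent predictors of clinical events". The embedded protocol's Statistical analysis has the same list. Section 3.12.2 (Additional analyses) is marked N/A.

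On what drives the count, section 3.4 says that, depending on IMR, "clinical status and the other complementary tests the physician will be able to modify the number of biopsies" set by each centre's protocol. Sections 2.1 and 3.3.1 and the embedded Biopsies and immunosuppressive therapy section agree: schedules differ by centre, and the physician also weighs clinical condition and other tests. On data, section 4.4 says "Sociodemographic, clinical, laboratory and follow-up data of each patient will be included" in the study database.

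**The concern.** The protocol accepts that confounding needs handling, but ties the adjustment to clinical events, which are secondary. A one-year biopsy count is not a time-to-event outcome, so the Cox model does not reach it. Followed as written, the methods leave the endpoint that carries the hypothesis with a raw contrast between groups formed by a measured value.

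The protocol names at least two other determinants of that count: the centre's own schedule and the patient's clinical state. Suppose clinically well patients tend to have lower IMR and also have fewer biopsies for clinical reasons, or low-IMR patients cluster in centres with lighter schedules. The unadjusted test could then show fewer biopsies in the low-IMR group although IMR changed nothing. At stake is a conclusion about reducing rejection surveillance.

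**Working it through.** **1. Which listed method fits the count?**

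| Method in 3.12.1 | Fits a two-group biopsy count? | Takes covariates? |
|---|---|---|
| t test / Mann-Whitney | yes | no |
| ANOVA / Kruskal-Wallis | for more than two groups | not as listed |
| Chi-square / Fisher | for categories only | no |
| Kaplan-Meier | for events | no |
| Cox regression | for clinical events | yes |

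No regression for a count or a continuous outcome is named.

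**2. The plan's own figure.** The only number is 100 patients at analysis, a feasibility figure: 8 centres × 10 to 15 transplants = 80 to 120, and 8 × 12.5 = 100. The protocol gives no SD or effect size for the biopsy count and no correlation of IMR with other factors. Everything below is therefore an assumption, used to show a range.

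**3. Clinical state as confounder.** Assume 100 patients split 50:50, no IMR effect, a mean of 4 biopsies and residual SD 1. One SD of clinical risk changes the count by b, and risk correlates r with IMR. With a median split, the expected spurious difference is 2 × r × b × √(2/π) = 1.596 × r × b:
- r = 0.2, b = 0.5: 0.16 biopsies
- r = 0.3, b = 0.75: 0.36
- r = 0.4, b = 1.0: 0.64

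Check of the middle case: total SD ≈ √(1 + 0.75² + 1/12) = 1.28 (1/12 for rounding to whole biopsies). The standard error is 1.28 × √(2/50) = 0.257, and 0.36/0.257 = 1.40. The chance of exceeding the critical value 1.98 is about Φ(1.40 − 1.98) = 28%. Simulation (3000 trials per setting) of the two-sided 5% t test gives:

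| r | b = 0.5 | b = 0.75 | b = 1.0 |
|---|---|---|---|
| 0.2 | 10.8% | 13.9% | 19.1% |
| 0.3 | 18.7% | 28.5% | 36.7% |
| 0.4 | 26.7% | 48.3% | 61.1% |

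A linear model that includes the clinical variable gives 4.5 to 5.4%.

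**4. Centre schedule as confounder.** Assume 8 centres, mean schedule 5, within-centre SD 1 and no IMR effect. Let s be the SD of centre schedules, w the SD of centre shares with IMR below 15 (around 0.5), and ρ the strength of the link between a heavier schedule and a smaller low-IMR share. The expected spurious difference is about −(s × w × ρ)/0.25 × 7/8. For s = 1, w = 0.2, ρ = 0.7 this is −0.49, as simulated. False-positive rates of the t test:

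| s | w = 0 | w = 0.1, ρ = 0 | w = 0.1, ρ = 0.7 | w = 0.2, ρ = 0 | w = 0.2, ρ = 0.7 |
|---|---|---|---|---|---|
| 0.5 | 5.0% | 6.5% | 9.6% | 8.4% | 20.6% |
| 1 | 4.4% | 7.9% | 15.0% | 13.9% | 40.2% |
| 2 | 5.5% | 9.4% | 23.5% | 20.2% | 55.7% |

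At ρ = 0.7 the spurious difference runs from −0.12 to −0.97 biopsies. Mann-Whitney behaves alike (4.4 to 53.4% over the grid). With centre in the model the rate is 4.5 to 5.9% and the bias about zero. If the IMR mix is the same in every centre, the unadjusted test is sound on this account.

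**The case against.** **This is analysis-plan content.** A covariate list may properly sit in a separate SAP, and the methods paragraph forbids no regression. That stands, and the absent list is not the point. The point is that the protocol does allocate adjustment, and allocates it away from its own primary endpoint.

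**No test is assigned to the biopsy count by name.** This also stands. A reader might infer that the protocol prescribes an unadjusted primary test. It does not say so; the reading comes from the list of methods and from Additional analyses being N/A.

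**The size is assumed.** True: the correlations, the effect of clinical risk and the split have no source in the documents. Excluding haemodynamic instability and rejection before the IMR study may narrow the range of clinical risk. The return to about 5% after adjustment is partly by construction, because the simulated model receives the only confounder, measured without error. A reader might infer that the biopsy result will be badly biased; the documents support only that it can be.

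**Adjustment does not deliver the hypothesis.** This is the strongest objection, and it stands. Biopsies may be reduced only below 15, and no group is managed without IMR. Part of any low-versus-high difference is the rule at work. A reader might infer that an adjusted ratio would show that IMR guidance lowers biopsy use. A single-group design cannot show that. Adjustment removes one source of error from the contrast and leaves this limit in place.

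**Conclusion.** The concern holds in limited form. The protocol's only named adjusted analysis serves clinical events, while the listed methods that fit the hypothesis-bearing biopsy count are unadjusted in a non-randomised comparison. The protocol itself says that other factors move that count.

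Whether the raw difference is biased depends on whether centre schedule or clinical state is related to IMR, which the documents do not tell. Over the assumed ranges the false-positive rate runs from about 5% (no such relation) to about 60% (the strongest assumed), with spurious differences of up to roughly one biopsy. These figures illustrate vulnerability and do not forecast this study. The change is worth making because it is cheap and uses data already scheduled.

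**What to change.** Name the main biopsy comparison as a regression of first-year EMB number on IMR group: Poisson with robust variance and follow-up time as offset. Robust variance matters because counts that follow a schedule may vary less than Poisson counts. An alternative is to model performed minus centre-scheduled biopsies per patient.

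Adjust for:
- centre, or the centre's scheduled number;
- a short prespecified set recorded before or at the IMR study: echocardiographic function, laboratory tests, medication before the IMR result, and time from transplant to the IMR study.

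The timing of medication needs care. The schedule collects it at months 1 to 2, the IMR study falls between the first and third month, and section 3.3.1 lets the IMR result influence immunosuppression. A value recorded after the result should not be a covariate.

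Report the adjusted estimate with its 95% CI and keep the t or Mann-Whitney result as supportive. State that, with no group managed without IMR and reduction allowed only below 15, the adjusted contrast describes how biopsies differ under IMR-informed care and does not by itself show a reduction against usual care.

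Cost: analysis wording and one more model. Laboratory, echocardiographic and medication data are already scheduled; the centre's scheduled number must be recorded if it is used. The adjusted reduction may be smaller or less precise than the raw one.

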## 2.3. Trial design

The IMR-HT study is a multicenter, prospective study aimed to guide post-HT management based on IMR. It will enroll consecutive eligible patients who undergo HT in each participation center. Patients undergoing HT will be screened for enrollment. Eligible patients will be informed about the study and will have to provide informed consent prior to being included. The recruitment period of the study is two years.

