**- Secondary outcomes:**

-IMR variation between first three months after HT and one year: Comparison between the values of index of microvascular resistance (IMR) measured by bolus thermodilution technique between the first and 3rd month after HT and one year in the invasive physiological study. IMR may be expressed as mmHg·s.

-Acute cellular rejection: A ≥2R degree according to the 2010 ISHLT system. Two or more focal infiltration points associated with myocyte injury in EMB. Diffuse infiltration with multi-focal myocyte injury with/without oedema, hemorrhage or vasculitis.Time frame: One year.

-Cardiac allograft vasculopathy: Accelerated fibroproliferative process characterized by diffuse, concentric and longitudinal thickening of the intima of the vascular tree of the graft, affecting everything from the major epicardial arteries to the coronary microvasculature.Time frame: 5 years.

-Cardiovascular mortality:Caused by cardiovascular disease or unknown death. Time frame: 5 years.

-Heart failure: Diastolic or systolic heart failure after heart transplant. Time Frame: Five years.

-Inmunosupressive therapy: Changes in any of the inmunosuppresive agents pre-established in each center heart transplant protocol. Time Frame: Five years

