## 3.6. Sample size

## 3.7. Recruitment

In 2023, around 325 heart transplants (HT) were performed in Spain Given a median of 10-15 HT per center and considering that eight centers that routinely perform invasive coronary physiology are participating, data will be analyzed when 100 patients have completed first year follow-up.

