**STUDY VARIABLES**

| **Event** | **Screening** | **1-2 month(s)**  **post-transplantation** | **12 months**  **post-transplantation** | **Annual**  **for 5 years** |
| --- | --- | --- | --- | --- |
| **Criteria** **for**  **inclusion/exclusion** | X |  |  |  |
| **Informed**  **consent** | X |  |  |  |
| **Laboratory test** | X | X |  |  |
| **Echocardiogram** | X | X | X |  |
| **Medication** | X | X | X |  |
| **Functional invasive coronary test** |  | X | X |  |
| **Events during**  **follow-up** |  |  | X | X |

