***Data and follow-up***

Clinical conditions, laboratory findings and clinical events will be assessed at one month and one year. Data will be included in an online database specifically designed for the study on platform REDCap (Research Electronic Data Capture).

A number will be assigned to each patient; their identity will not be disclosed in any case. All shared information will be anonymized. The principal investigator at each center will be responsible for keeping the data anonymized.

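### The figure of 100 is both the target sample size and the number who must complete year one, with no allowance for loss; and the five-year immunosuppression outcome has no scheduled medication data after month 12

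*Protocol*

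**What the plan says.** **Size and trigger.** The registration table in section 1 reads "Target sample size | 100". No text stands under section 3.6 (Sample size). Section 3.7 (Recruitment) says "eight centers that routinely perform invasive coronary physiology are participating, data will be analyzed when 100 patients have completed first year follow-up", and section 3.12.1 repeats that "data will be analyzed when 100 patients have completed first year follow-up". Section 3.12.3 (Analysis population and missing data) is marked not applicable. Section 3.12.1 names Kaplan-Meier curves and Cox regression for events.

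**Five-year outcomes.** Section 3.4 gives cardiac allograft vasculopathy, cardiovascular mortality, heart failure and immunosuppressive therapy a five-year time frame. The last is defined as "Changes in any of the inmunosuppresive agents pre-established in each center heart transplant protocol. Time Frame: Five years". In the study protocol reproduced under section 5.3.1, the Summary table plans follow-up at one year and then annually to five years, and Endpoints says that every endpoint is evaluated on that timetable.

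**Schedule.** The Study variables table has four columns: screening, months 1-2, month 12, and annually for 5 years. Its medication row reads "Medication | X | X | X", with the annual cell empty. Its row for events is marked at month 12 and annually. Section 3.10.2 and Data and follow-up both say "Clinical conditions, laboratory findings and clinical events will be assessed at one month and one year".

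**The concern.** A sample size counts patients entered; a completion trigger counts those still there a year later. The two can be equal only if nobody is lost. That is unlikely here, since the Introduction and Rationale describes acute rejection as the leading cause of death and re-transplantation, above all in year one.

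The trigger also leaves a decision open that affects the results. If completing means being alive with the original graft at month 12, and the analysis is then run on those 100, first-year mortality in that set is zero by construction. The Introduction and Rationale asks whether management can be safely modified on IMR, so the handling of early deaths should not be left open.

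The five-year outcomes raise a different question: whether the schedule collects what they need, and when they would be analysed. A site that follows the visit table as printed would record no scheduled medication data in years 2 to 5.

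**Working it through.** **1. Where 100 may come from.** The protocol states no power, effect size, standard deviation, event rate or loss rate, so no sample-size formula can be reproduced. Only a feasibility count is possible. Inputs: 8 centres and "Given a median of 10-15 HT per center" (section 3.12.1; the period is not stated and is read here as one year). 8 × 10 = 80 and 8 × 15 = 120, with midpoint 100. So 100 is compatible with one year's throughput, though the protocol does not say that it was derived this way.

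**2. What loss does to a target equal to the trigger.** Let d be the proportion enrolled who do not count as completing year one. The protocol gives no d, so the values are assumptions. Losses are taken as independent.

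- Expected completers among 100 = 100 × (1 − d)
- Enrolment needed to expect 100 completers = 100 / (1 − d), rounded up
- Chance that all 100 complete = (1 − d)^100
- Enrolment for a 90% chance of at least 100 completers = smallest N with P(Binomial(N, 1 − d) ≥ 100) ≥ 0.90

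| d (assumed) | Completers of 100 | Enrol to expect 100 | Chance all 100 complete | Enrol for 90% chance |
|---|---|---|---|---|
| 1% | 99 | 102 | 37% | 102 |
| 2% | 98 | 103 | 13% | 104 |
| 5% | 95 | 106 | 0.6% | 108 |
| 10% | 90 | 112 | 0.003% | 116 |
| 15% | 85 | 118 | below 0.001% | 124 |
| 20% | 80 | 125 | below 0.001% | 132 |

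**3. Whether a larger enrolment is feasible.** Section 2.3 says "The recruitment period of the study is two years". Over two years the pool is 8 × 10 × 2 = 160 to 8 × 15 × 2 = 240 transplants. Enrolling 112 needs 112/240 = 47% to 112/160 = 70% of them; enrolling 125 needs 52% to 78%. The pool is large enough in number, so the fault lies in how the figure is stated.

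**4. Follow-up available at the named cut.** Section 1 dates enrolment from 25 March 2024. If 100 patients accrue evenly over two years, the last reaches month 12 about 25 March 2027. Follow-up then runs from 1 to 3 years, mean about 2. If every transplant were enrolled, at 80-120 a year, the 100th would enter at 100/120 = 0.83 to 100/80 = 1.25 years. The cut would then fall at 1.83 to 2.25 years, which is also the longest follow-up. In neither case does any patient have five years. With full two-year recruitment, the last five-year visit is about 25 March 2031.

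**5. The schedule statements side by side.**

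| Item | Outcome or evaluation plan | Collection plan |
|---|---|---|
| Immunosuppressive therapy | Five years (section 3.4); all endpoints annually to year 5 (Endpoints) | Medication at screening, months 1-2 and month 12; annual cell blank (Study variables) |
| Clinical events | Five years for vasculopathy, cardiovascular death and heart failure (section 3.4); annually to year 5 (Summary, Endpoints) | Annual column marked (Study variables), but one month and one year in section 3.10.2 and Data and follow-up |
| Data cut for five-year results | Five-year time frames (section 3.4) | Only the year-one trigger is named (sections 3.7, 3.12.1) |

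**The case against.** A reader might infer that the plan analyses only patients who survive year one, and that the five-year endpoints cannot be delivered. Neither follows from the text.

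- **Survivors only.** The trigger sentence fixes when data are analysed, not who is analysed. Kaplan-Meier and Cox methods can include first-year deaths, and a patient who dies may be meant to count as having completed. Analysis sets are also commonly detailed in a statistical analysis plan, which is not at hand. What stands is narrower: completion is undefined, and section 3.12.3 marks the analysis population not applicable, so a completers-only reading is open.
- **Five-year endpoints.** The Summary, Endpoints and Study variables all plan annual event follow-up to year 5, which covers vasculopathy, cardiovascular death and heart failure. For these, the defect is conflicting assessment times and an unnamed cut. Only medication has an empty annual cell. Even there, the Endpoints sentence implies an intention to evaluate it, so the two passages conflict.
- **Is 100 a cap?** The section 1 entry is a registry field. It could mean the evaluable number, with consecutive enrolment continuing until 100 complete. Patients found ineligible at the physiological study, through earlier rejection or significant epicardial lesions, need not count as enrolled losses, because section 2.3 separates screening from inclusion. This is fair, and it is why the shortfall is stated as conditional on stopping at 100. It does not remove the need to say which number 100 is.

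**Conclusion.** The point holds in a limited form.

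- **Size.** The same 100 serves as target and as completion trigger, with no loss allowance. If enrolment stops at 100, one patient not counted as completing is enough to leave the trigger unmet. Assumed losses of 5-20% give 80-95 expected completers, or 106-125 to be enrolled. Those rates are assumptions. The feasibility figures also assume that the 10-15 transplants per centre are annual.
- **Analysis set.** A completers-only analysis is permitted, not stated. The loss of first-year deaths from the mortality and composite results is therefore a risk conditional on that reading. How it would change the association between IMR and events has not been shown.
- **Five-year outcomes.** The immunosuppression outcome conflicts with the medication schedule as printed. Event follow-up to year 5 is planned, but two sections list only one month and one year. No patient can have five years of follow-up at the only named cut. It does not follow that five-year event results are ruled out.

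The study can go ahead, but these passages should be reconciled before the first analysis.

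**What to change.** 1. In section 1, restate the target as 100 patients with a valid baseline IMR. Under section 3.6, give the expected number enrolled separately, with the loss assumption behind it.
2. In sections 3.7 and 3.12.1, set the first analysis at the time when the 100th such patient has reached 12 months after transplant, died or been re-transplanted. Say how withdrawals are counted.
3. In section 3.12.3, replace the not-applicable entry with a statement that all enrolled patients with a baseline IMR are analysed, including those who die in year one.
4. In Study variables, mark medication in the annual column.
5. Reconcile section 3.10.2 and Data and follow-up with the annual timetable in Summary, Study variables and Endpoints.
6. Name a later data cut for the five-year outcomes.

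The cost is wording and one annual field in the database. The main drawback is that, with the trigger counting deaths and re-transplants, the stated number of true first-year completers will be somewhat below 100. Shortening the five-year time frames to one year would also remove the conflict, but it would discard follow-up that the protocol already plans, so adding the field and the cut is preferable.
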